## Methods and Materials

### Trial Design

WALNUTs (WSS) is a multi-school, parallel (two-group), controlled, 6-month superiority randomized clinical trial in a large population-based sample aiming to include 800 healthy teenagers in Barcelona, Spain. After data collection, 771 participants were equally randomized in two groups (386/385), but because of some exclusions post-randomization, 748 were finally included. Study subjects were randomly assigned to two intervention groups just after baseline assessments: the walnut group (*n* = 370, consuming walnuts daily and advised to follow general healthful eating recommendations, such as eating a piece of fresh fruit every day) or control group (*n* = 378, not consuming walnuts and advised also to follow the same general healthful eating recommendations). They were assessed at baseline and after the intervention by several internationally validated neuropsychological tests and behavioral rating scales. Due to the project's budget limitations, a random subsample of 200 adolescents per group of intervention (*n* = 400) were targeted to measure changes in omega-3 PUFA biomarkers. We finally got 270 participants, 139 in the walnut group and 131 in the control group. All participants randomized to the walnut group received 30g/day of kernel walnuts to be incorporated into their diet for free. The type of walnuts selected, Californian walnuts, is estimated to contain about 9 g of ALA per 100 g (20, 21). There is evidence that young Spanish subjects between 10–13 and 14–17 years of age consume on average 5.7 g (SD 24.5 g) and 6.1 g (SD, 20.8 g) of nuts daily (22), which supports the feasibility of our trial design. Figure 1 shows the project's design and structure.

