### Sample Size

Prior to data collection, the statistical power of the study for neuropsychological outcomes was based on 400 participants per group. Six primary outcomes were considered: the N-back task, the Attention Network Test (ANT), the Tests of Primary Mental Abilities (PMA-R, the Spanish adaptation), the Roulettes Task (adapted from the Cups Task), the Strengths and Difficulties Questionnaire (SDQ), and the Attention Deficit Hyperactivity Disorder (ADHD) DSM-IV form list. The cognitive outcomes with mean values of 100 (SD 15) units corresponding to the standard values of neuropsychological scores in the general population (23) were considered, with a correlation between them of 0.25. The targeted intervention effect was a change of 3 units, based on previous studies in adult samples (16, 18). We considered a type I error of 0.05 and corrected calculations for multiplicity using the Benjamini-Hochberg method. A 10% loss of follow-up was assumed. Additionally, we assumed that the final models had an R^2^ of 20%. With all these considerations, the study would have 95% power to detect the effect with at least one outcome, 90% to detect the effect with at least two, 80% to detect the effect with at least 3, 70% to detect the effect with at least 4, 55% to detect the effect with at least 5, and 31% to detect the effect with all six outcomes. Similar power calculations can be made from the final participation sample of 748 participants.

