### Procedures

#### Recruitment and Randomization

An experienced fieldwork technician with the help of two more experts recruited participants in collaboration with the Barcelona school system. We first obtained permission from the boards of several schools in Barcelona to inform them about the trial. Then, we provided the schools with a recruitment fllier to assess willingness to collaborate and grant us permission to contact interested families by telephone. Families interested in participating contacted us through the school and filled out a form with their telephone number. Trained personnel contacted the parents and explained the study in detail. Fieldworkers verified the eligibility criteria of each candidate. We performed age-, gender-, and maternal education-stratified random computerized sampling within each school to assign adolescents to one of the two groups. In order to avoid contamination, we gave the walnuts for free to the corresponding group and asked participants to consume them at home.

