## Data Analysis

Descriptive statistics (frequencies, means, standard deviations for normally distributed data; medians and interquartile ranges for nonparametric data) will be used to describe the baseline characteristics of the walnut and control groups. To assess the effect of the intervention on brain development, we use multivariable linear regression models. Similar regression models will be used to assess the effect of the intervention on red blood cell PUFA proportions, particularly ALA, as outcome variables. To assess the proportion of the effect of the intervention on brain development that is mediated by red blood cell PUFA changes, results will be compared in models with and without the mediator. All analyses will be based on the intention to treat in order to estimate the effectiveness of a public health recommendation (i.e., to encourage eating 30 g of walnuts per day). We also plan to conduct a per-protocol analysis with those who comply with the intervention, i.e., single days of reporting eating walnuts (≥ 100 days during 6 months) (34). The nominal statistical significance will be set at the *P* < 0.05 level (two-sided) for the primary outcomes. Statistical analyses are performed with STATA. A detailed statistical analysis plan will be established before database lock and any analyses.

Using multiple primary endpoints, the study will be considered successful if the results of either one of the primary endpoints is statistically significant in favor of the experimental treatment and/or treatment adherence. In this case, we will report for each primary endpoint a nominally significant level and the corrected *p*-value determined by the method for multiplicity adjustment.

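### The article promises intention to treat for every analysis but carries forward 748 of 771 randomised participants; the 23 removed after allocation came about twice as often from the walnut arm

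*Protocol article*

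**What the plan says.** Three sections of the protocol article bear on the analysis set.

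- **Trial Design** gives the number allocated, "771 participants were equally randomized in two groups (386/385", and continues "but because of some exclusions post-randomization, 748 were finally included". It then gives the assigned groups by their sizes after exclusion: "the walnut group (*n* = 370, consuming walnuts daily" and "control group (*n* = 378, not consuming walnuts".
- **Sample Size** closes with "Similar power calculations can be made from the final participation sample of 748 participants".
- **Data Analysis** states: "All analyses will be based on the intention to treat in order to estimate the effectiveness of a public health recommendation". It plans a separate per-protocol analysis of compliers and leaves detail to a statistical analysis plan that is to be fixed before database lock.

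The text does not say why the 23 were removed, when, or by whom. No section names a modified intention-to-treat set or says that the 23 will be analysed.

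**The concern.** Intention to treat means that participants are compared in the groups to which chance assigned them. Removing some after allocation gives up part of that protection, and an unequal removal gives up more.

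Two features of this trial make the point more than formal. Participants could not be blinded, and only the walnut arm had a daily food to eat and weekly consumption to report. So whether someone was excluded after allocation could depend on arm. The target effect is also small, 3 units on a scale with SD 15 (3/15 = 0.2 SD), and success may rest on any one of six primary endpoints. A modest shift could matter for a borderline result.

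**Working it through.** **Inputs.** Randomised: 771, split 386/385, with the arm that had 386 not stated (Trial Design). Included: 370 walnut, 378 control (Trial Design). Target effect 3 units, SD 15 (Sample Size).

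**Step 1, reproduce the totals.** 386 + 385 = 771. 370 + 378 = 748. 771 − 748 = 23 excluded, and 23/771 = 3.0%.

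**Step 2, exclusions by arm under both readings.**

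| Reading | Walnut excluded | Control excluded | Ratio of counts | Fisher exact p |
|---|---|---|---|---|
| Walnut had 386 | 386 − 370 = 16 (4.1%) | 385 − 378 = 7 (1.8%) | 2.3 | 0.088 |
| Walnut had 385 | 385 − 370 = 15 (3.9%) | 386 − 378 = 8 (2.1%) | 1.9 | 0.145 |

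The walnut arm lost about twice as many under either reading. Neither p-value is below 0.05.

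**Step 3, possible shift in the treatment effect.** Let D be the amount, in SD units, by which the excluded differ from the retained. The mean of a whole arm differs from the mean of its retained members by (excluded/randomised) × D. The gap between the effect in 771 and the effect in 748 is therefore

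shift = 15 × [(walnut excluded/walnut randomised) × D(walnut) − (control excluded/control randomised) × D(control)].

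The documents give no value for D, so 0.5 to 1 SD is an assumption. It has to refer to 6-month change, because the endpoints are changes from baseline (Neuropsychological and Behavioral Testing); a difference in level already present at baseline would largely cancel. The documents give no SD for change, so 15 units is also assumed to apply to it.

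*Same D in both arms*
- 16 v 7: 15 × (16/386 − 7/385) × 0.5 = 0.17 units; with D = 1, 0.35 units.
- 15 v 8: 15 × (15/385 − 8/386) × 0.5 = 0.14 units; with D = 1, 0.27 units.
- Range 0.14 to 0.35 units, which is 5 to 12% of the 3-unit target.

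*Only the walnut exclusions selective, D(control) = 0*
- 16 excluded: 15 × 16/386 × 0.5 = 0.31 units; with D = 1, 0.62 units.
- 15 excluded: 15 × 15/385 × 0.5 = 0.29 units; with D = 1, 0.58 units.
- Range 0.29 to 0.62 units, which is 10 to 21% of the target.

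As an outer case, opposite directions in the two arms would give 0.45 to 0.90 units under the same D.

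**Step 4, set the sections side by side.** Data Analysis gives no number for its intention-to-treat set. The only final set that the article names is 748, in Trial Design and again in Sample Size, and Trial Design presents 370 and 378 as the assigned groups. If that set is analysed, it is not all participants as randomised. If all 771 are to be analysed, the article does not say so.

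**The case against.** The strongest reply is that no sentence equates 748 with the intention-to-treat set. Data Analysis names no number, the mention in Sample Size is only a remark on power, and exact set definitions commonly sit in the statistical analysis plan, which is not shown. This stands as far as it goes: that the article calls the 748 intention to treat is something a reader might infer, not something it states. It does not remove the point, which is a conflict within this document and not a missing detail.

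Second, the reasons may be benign. The eligibility list is long, some of the 23 may have been found ineligible late, and Figure 1, which is not shown, may account for them. On the other side, "Fieldworkers verified the eligibility criteria of each candidate" comes before the description of assignment, so late ineligibility is not the evident explanation. Neither account can be confirmed. A reader might also infer that the walnut regimen drove the exclusions. The text does not support that: it gives no reasons, the imbalance could be chance, and the Discussion says that those doing the statistical analyses are blinded.

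Third, the share is small and the size of any bias rests on an assumed difference. That is correct, and large bias is not shown.

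Fourth, imputation under missing at random adds little for participants with baseline data only, and cannot by itself repair selection that depends on arm. This also stands, and it is why the fix asks for more than imputation.

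**Conclusion.** The point holds as a conflict between the promise of intention to treat and the carrying forward of 748 of 771 randomised participants. What is certain is the count: 23 removed (3.0%), 16 v 7 or 15 v 8, with the walnut arm losing about twice as many on either reading. That the 748 will be the primary set is an inference, though the natural one. That exclusion depended on arm is possible and unproven.

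The shift of 0.14 to 0.35 units, or 0.29 to 0.62 if only walnut exclusions were selective, rests entirely on the assumed 0.5 to 1 SD difference in 6-month change and on 15 units as the SD of that change. Severity moderate, confidence moderate.

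**What to change.** In the statistical analysis plan, before database lock:

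1. Define the primary intention-to-treat set as all 771 participants in the arm to which they were randomised. Baseline tests preceded randomisation, so baseline data should exist for the 23. Use these and any 6-month data, where consent permits.
2. State the missing-data method, and add a sensitivity analysis in which the unobserved outcomes are not missing at random and may differ by arm.
3. Allow exclusion from the primary set only for ineligibility established from information dating from before randomisation and judged blind to arm.
4. Label the analysis of the 748 as modified intention to treat and report it as a sensitivity analysis.
5. Report the reasons for the 23 exclusions by arm, and state which arm had 386.

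The cost is up to 23 records restored, a few imputed outcomes, a paragraph in the plan and slightly more analysis work. Some records may not be recoverable, depending on consent and 6-month status, which the article does not give.

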**Figure 1 F1:**
[figure not shown]
Project design and structure.

### Eligibility Criteria

The participants eligible were adolescents aged between 11 and 16 years attending regular schools in Barcelona. Originally, the study protocol was designed to recruit adolescents aged 12–15 years; however, the schools facilitated participant recruitment through the classes, and there were children a bit younger and older that we did not want to exclude if they were willing to participate in the study. Exclusion criteria include those consuming supplements of omega-3 PUFAs regularly, eating walnuts on a daily basis, and/or having an allergy to walnuts and/or gluten. Subjects were excluded also if they reported lactose intolerance or an allergy to cereals, dried fruits, peanuts, soy, sesame, or sulfites, since the walnut industry manipulates these products and there could be traces of them in the walnut packages. Eligible candidates who were siblings of family units were randomized and allocated to the same group and analyzed as clusters.

### Sample Size

Prior to data collection, the statistical power of the study for neuropsychological outcomes was based on 400 participants per group. Six primary outcomes were considered: the N-back task, the Attention Network Test (ANT), the Tests of Primary Mental Abilities (PMA-R, the Spanish adaptation), the Roulettes Task (adapted from the Cups Task), the Strengths and Difficulties Questionnaire (SDQ), and the Attention Deficit Hyperactivity Disorder (ADHD) DSM-IV form list. The cognitive outcomes with mean values of 100 (SD 15) units corresponding to the standard values of neuropsychological scores in the general population (23) were considered, with a correlation between them of 0.25. The targeted intervention effect was a change of 3 units, based on previous studies in adult samples (16, 18). We considered a type I error of 0.05 and corrected calculations for multiplicity using the Benjamini-Hochberg method. A 10% loss of follow-up was assumed. Additionally, we assumed that the final models had an R^2^ of 20%. With all these considerations, the study would have 95% power to detect the effect with at least one outcome, 90% to detect the effect with at least two, 80% to detect the effect with at least 3, 70% to detect the effect with at least 4, 55% to detect the effect with at least 5, and 31% to detect the effect with all six outcomes. Similar power calculations can be made from the final participation sample of 748 participants.

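### The six printed power figures (95/90/80/70/55/31%) do not follow from the stated inputs, which give about 98/96/93/86/73/48%

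*Protocol article*

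**What the plan says.** The Sample Size section gives a complete set of planning inputs:

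- Sample: "the statistical power of the study for neuropsychological outcomes was based on 400 participants per group", with 10% loss to follow-up.
- Endpoints: "Six primary outcomes were considered".
- Scale: "The cognitive outcomes with mean values of 100 (SD 15) units corresponding to the standard values of neuropsychological scores in the general population", "with a correlation between them of 0.25".
- Effect: "The targeted intervention effect was a change of 3 units".
- Error control: type I error 0.05, corrected by Benjamini-Hochberg.
- Model: "we assumed that the final models had an" R² of 20%.

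It then states that, taking all of this into account, "the study would have 95% power to detect the effect with at least one outcome, 90% to detect the effect with at least two", 80% for at least three, 70% for at least four, "55% to detect the effect with at least 5, and 31% to detect the effect with all six outcomes". It adds that the final sample of 748 allows similar calculations.

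The Data Analysis section sets two-sided testing at 0.05. It counts the study as successful if any one primary endpoint is significant.

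**The concern.** The SD of 15 is described as a general-population value, so it is an SD before covariate adjustment. A model R² of 20% lowers the residual SD and must raise power. If the printed figures already arise at SD 15 without that gain, the text and the numbers describe different calculations.

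The section also never says how many outcomes are assumed to move. A figure of 31% for all six makes sense only if all six do. Success requires only one, so a reader interpreting a null result will look at the 95% and needs to know which scenario it describes.

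**Working it through.** **Inputs.** All are from Sample Size, except two-sidedness (Data Analysis) and the final group sizes (Trial Design).

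- Evaluable per group: 400 × 0.90 = 360.
- Effect: 3 units on every outcome.
- SD without adjustment: 15. Residual SD with R² 20%: 15 × √(1 − 0.20) = 13.42.
- Correlation between outcomes: 0.25, applied to the test statistics.
- Six tests, two-sided, Benjamini-Hochberg at 0.05.

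**Expected test statistic per outcome.** Effect ÷ (SD × √(2/n)), with √(2/360) = 0.07454.

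- With R²: 3 ÷ (13.42 × 0.07454) = 3.00.
- Without R²: 3 ÷ (15 × 0.07454) = 2.683.

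**Method.** Draw six normal test statistics with these means and pairwise correlation 0.25, convert to two-sided p-values, apply the step-up procedure and count rejections (1,000,000 draws). Percentages with at least k rejections, all six outcomes truly moving:

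| Calculation | ≥1 | ≥2 | ≥3 | ≥4 | ≥5 | 6 |
|---|---|---|---|---|---|---|
| Printed | 95 | 90 | 80 | 70 | 55 | 31 |
| Closest reproduction under Benjamini-Hochberg: 360 per group, SD 15, no R² | 95.4 | 90.5 | 83.3 | 72.5 | 55.9 | 31.5 |
| All stated inputs, R² 20% | 98.4 | 96.4 | 92.7 | 85.9 | 73.0 | 47.9 |
| All stated inputs minus printed | 3.4 | 6.4 | 12.7 | 15.9 | 18.0 | 16.9 |
| R² kept, Benjamini-Yekutieli instead | 95.6 | 90.4 | 82.8 | 71.1 | 53.8 | 29.3 |
| No R² and no loss (400 per group) | 97.0 | 93.6 | 88.2 | 79.1 | 63.9 | 38.7 |

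With every stated input, no printed figure is matched. Without R², four of the six agree within 1 point. The figures for at least three and at least four come out 3.3 and 2.5 points above the printed 80 and 70. Leaving out the 10% loss as well worsens the fit, so under Benjamini-Hochberg the printed series looks as if it contains the loss but not the R² gain.

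**Sensitivity to the correlation.** If 0.25 describes the raw scores, the residual correlation could differ. With R² kept, a residual correlation of 0.05 gives 99.8/99.1/96.8/90.1/73.4/40.2, and 0.35 gives 97.2/94.6/90.7/84.4/73.2/51.5. Neither recovers the printed series.

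**Fewer outcomes truly affected.** Chance of rejecting at least one truly affected outcome:

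- One affected: about 65% with R², 52% without.
- Two affected: about 85% with R², 74% without.

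Counting any rejection, false positives included, gives 66% and 54% for one affected outcome. With five affected, power for all six is about 2% without R² (2.6% with).

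**Final sample, 370 and 378, no further loss.** 98.7/96.9/93.7/87.7/75.7/50.9 with R²; 96.0/91.7/85.1/74.8/58.9/34.1 without.

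**The case against.** The cause cannot be read from the article. It is tempting to infer that R² was simply forgotten, and that is the simplest explanation. But Benjamini-Yekutieli with R² kept fits about as well, and R² kept with the effective sample divided by 1.25 gives the no-R² series exactly, because 1/0.8 = 1.25. This stands. The section names Benjamini-Hochberg and no design effect, however, so the text and the figures disagree on any of these explanations.

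The discrepancy is also on the safe side. Under the stated inputs power is higher than printed throughout, the success rule depends only on the at-least-one figure (3 points off), and data collection is over. This also stands, and it limits the consequence without removing the contradiction.

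A reader might go further and call the 95% far too optimistic because success needs only one endpoint. The documents do not support that. A common effect on all outcomes is a conventional planning scenario, the all-six figure implies it, and nothing says the trial is aimed at a benefit in one or two domains only. Nor does the at-least-one figure strictly need all six: four affected outcomes give 96.0% with R², and five give 93.6% without. The all-six condition is an unstated assumption, not an arithmetic error.

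A reader might likewise infer that the remark about 748 participants hides a loss of power. Reaching a clearly lower series requires a further 10% loss from a sample described as finally included. Without it, the no-R² figures are slightly above the printed ones, so calling the calculation similar is acceptable.

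**Conclusion.** The inconsistency is real and should be corrected in the text. The printed 95/90/80/70/55/31% is not the power that the stated inputs produce, which is about 98/96/93/86/73/48%. The gap is 3 points for at least one outcome, 6 for at least two, and 13 to 18 for at least three up to all six, always with the printed value too low.

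This rests on reading R² as a reduction in residual variance from SD 15, two-sided tests, normal test statistics with correlation 0.25, and a true 3-unit effect on every outcome. That R² was left out is consistent with the figures but not established. The planned sample is not shown to be inadequate.

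**What to change.** Confirm which inputs were actually used, then do one of two things:

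- Keep the R² assumption and restate the series as about 98/96/93/86/73/48%.
- Remove the R² statement and restate the series as about 95/90/83/72/56/31%. Deleting the statement alone is not enough, because the printed 80 and 70 would still be about 3 points low.

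If a different multiplicity correction or another reduction was used, name it and check the figures against it.

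State that the series as a whole assumes a true 3-unit effect on all six outcomes. Since one significant endpoint suffices for success, it would be useful to add the chance of detecting a truly affected outcome: about 65% (52% without R²) if one moves, 85% (74%) if two move.

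Figures for the final sample are optional. If given, 370 and 378 with no further loss yield about 99/97/94/88/76/51% with R², or 96/92/85/75/59/34% without.

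The cost is a few sentences. Design, data and analysis are unaffected.
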